#### Data management and monitoring

Identifiable data will be locked in a filing cabinet in the Leeds Institute of Rheumatic and Musculoskeletal Medicine (LIRMM) research offices or held in an encrypted file stored on a password-protected University of Leeds server, with access limited to the study team. Pseudonymised data will be entered onto a password-protected access database, developed in line with the LIRMM Data Quality Management System Standard Operating Procedures. Data will be periodically internally verified and audited. Data will be stored in a deidentified manner for 5 years after the final publication.

Physiotherapists will record the time taken to administer and lead the Group E-Rehab exercise classes and if a trial physiotherapist is contacted by a My Knee UK participant for help or advice, this will also be recorded. These data will contribute to estimating the cost of delivering the Group E-Rehab and My Knee UK interventions.

Descriptive data relating to exercise adherence relevant to each treatment arm will be collected at the end of the 12-week intervention phase. The web analytics service Google Analytics^38^ will be used to record the number of times each participant accesses the My Knee UK website and the duration of their website access. The weekly number of home-based exercise sessions completed (self-reported in response to the automated SMS message) will also be recorded. Group E-Rehab data will include the number of Zoom exercise classes attended and the number of Sway educational sessions accessed, along with the time spent engaged with each session.

#### Nested qualitative study

A subsample of consenting participants, purposively sampled by age, sex and having received the My Knee UK or Group E-Rehab intervention, will undergo individual in-depth remote (videoconference or telephone) interviews where the acceptability of the two e-rehabilitation interventions will be explored. Interviews will focus on participants’ experiences of being in the trial and will comprise questions specific to each intervention. It is anticipated around 20 individuals will be interviewed with the final number being determined once data saturation has been reached, which will be when there is consensus among the research team that minimal new information is being generated. Participants will be interviewed either on completion of the 3-month follow-up questionnaire (visit 3), or at the end of follow-up on completion of the 9-month questionnaire (visit 4).

Semistructured videoconference interviews with the two physiotherapists who delivered the Group E-Rehab Zoom classes will be conducted. This is to gain insight about the preparation they received, thoughts about its acceptability, their experience of delivering the intervention and any barriers to delivering it effectively that they identified.

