### Trial data collection and outcomes

#### Follow-up visits

Follow-up postal questionnaires are sent out at 3 months (visit 3), which is the end of the intervention treatment period, and at 9 months (visit 4). Participants who withdraw from the trial early will not be replaced and will be requested to complete the next scheduled follow-up questionnaire. The schedule of enrolment and data collected during the trial is detailed in table 4.

**Table 4 T4:** Standard Protocol Items: Recommendations for Interventional Trials schedule of enrolment, interventions and assessments.

	Study period			
	Enrolment	Randomisation	Follow-up	Close-out
Timepoint	−1	0	3 months ±4 weeks	9 months ±4 weeks
Enrolment				
Initial contact and study information	X			
Eligibility screen	X			
Informed consent	X			
Allocation		X		
Interventions				
Group E-Rehab				
‘My Knee UK’ Group				
Control group (duration of treatment will be variable)				
Assessments				
Clinical information				
Age, gender, ethnicity		X		
Previous joint surgery		X		
Employment and physical activity		X		
Height and weight		X		
History of current knee pain		X		
General health and medication use		X	X	X
Patient-reported outcomes				
Joint pain manikin		X	X	X
Knee pain frequency (5-point scale)		X	X	X
Confidence and motivation to do exercises (11-point NRS)		X	X	X
Global change (7-point Likert scale)			X	X
WOMAC (Pain, function and stiffness)		X	X	X
ASES		X	X	X
HADS		X	X	X
Generic health status (EQ-5D-5L)		X	X	X
Health-related quality of life (SF-12)		X	X	X
Resource use			X	X

ASES, Arthritis Self-Efficacy Scale; EQ-5D-5L, European Quality of Life-Five Dimension-Five Level Scale; HADS, Hospital Anxiety and Depression Scale; NRS, numeric rating scale; SF-12, 12-Item Short Form Survey; WOMAC, The Western Ontario and McMaster Universities Osteoarthritis Index.

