#### Sample size

A total sample size of 90 participants (30 per arm), based on established principles for a feasibility study,^39^ will be adequate for evaluating feasibility and collecting sufficient data to inform the sample size in a definitive randomised controlled trial (RCT).

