### Feasibility trial outcome

Data from the feasibility trial and follow-up nested qualitative study will be integrated to support the case for determining whether one or both e-rehabilitation interventions are feasible, acceptable and have the potential to be implemented in practice. The qualitative and quantitative data will enable the potential for My Knee UK and/or Group E-Rehab to be introduced as alternative models of service delivery to be explored. The feasibility trial will be deemed successful if the results demonstrate that (1) participants and physiotherapists find one or both intervention(s) acceptable (using data from the nested qualitative study), (2) it is possible to calculate a manageable sample size for use in a definitive RCT, (3) attrition at visit 3 (3 months) is no more than 30% and (4) at least 40% of eligible patients are recruited to the trial. If one or both e-rehabilitation interventions are acceptable, the intention is to develop the protocol for and conduct a definitive RCT with a health economic component. This will be sufficiently powered for testing the wider use of My Knee UK and/or Group E-Rehab (depending on feasibility trial outcome) as a prescribed treatment for individuals with persistent knee pain.

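### The acceptability criterion rests on interviews that cannot reach participants who return no questionnaire and do not deliberately sample those who stop, so it is at risk of bias towards acceptability

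*Protocol article*

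**What the plan says.** Three parts of the protocol article bear on this point.

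- **Feasibility trial outcome.** The first of four success criteria is that "participants and physiotherapists find one or both intervention(s) acceptable (using data from the nested qualitative study"). It has no numerical threshold. The third criterion is that "attrition at visit 3 (3 months) is no more than 30" per cent. The other two concern a manageable sample size and the share of eligible patients recruited. The intention to go on to a definitive trial is also tied to acceptability.
- **Nested qualitative study.** The subsample is "purposively sampled by age, sex and having received the My Knee UK or Group E-Rehab intervention". On timing, "Participants will be interviewed either on completion of the 3-month follow-up questionnaire (visit 3"). A second, later interview point is given as the only other option: "or at the end of follow-up on completion of the 9-month questionnaire (visit 4"). On number, "It is anticipated around 20 individuals will be interviewed", with the final count set by saturation as agreed within the research team. The two physiotherapists who ran the Group E-Rehab classes are interviewed as well.
- **Follow-up visits.** "Participants who withdraw from the trial early will not be replaced and will be requested to complete the next scheduled follow-up questionnaire".

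**The concern.** People who gave up on a remote exercise programme are the best source on why it was unacceptable. The published rule fixes who can be interviewed (by age, sex and arm) and when (after a returned questionnaire). Neither part refers to how far the person engaged with the programme. Saturation does not repair this: the team can agree that little new is emerging from engaged returners without having heard a disengaged one.

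What is at stake is a go/no-go decision. If the interviews lean towards people who stayed, criterion (1) may be met for a programme that a sizeable minority abandoned. The barriers that a definitive trial should address would then go unheard. The gap matters most for My Knee UK. It is unsupervised, and no delivering physiotherapist is interviewed about it, so its interview evidence comes from participants alone.

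**Working it through.** **Inputs**

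- Randomised: "A total sample size of 90 participants (30 per arm"), from Sample size. Check: 3 × 30 = 90, which agrees. The two intervention arms hold 2 × 30 = 60.
- Attrition allowed at 3 months: 30%, from Feasibility trial outcome.
- Participant interviews: about 20, from Nested qualitative study.
- Assumptions of mine: attrition means no returned 3-month questionnaire, and it is equal across arms.

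**Step 1. Who can reach an interview**

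| Participant in an intervention arm | Route to interview | Deliberately sampled? |
|---|---|---|
| Follows the programme and returns a form | Yes | By age, sex and arm |
| Stops the programme, stays in follow-up, returns a form | Yes | No; enters by chance |
| Withdraws early, returns the next form as requested | Yes | No; enters by chance |
| Misses the 3-month form, returns the 9-month form | Yes, about six months after the programme ended | No; enters by chance |
| Returns neither form | None | No |

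**Step 2. Size of the group outside the 3-month frame**

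Number outside = 60 × d, where d is the share with no 3-month questionnaire. A sample of 20 drawn in proportion from all 60 would include 20 × d of them; the 3-month route includes none.

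| d | Outside | Left in frame | Expected among 20 if proportional |
|---|---|---|---|
| 10% | 6 | 54 | 2 |
| 20% | 12 | 48 | 4 |
| 30% | 18 | 42 | 6 |

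The figure of 18 is a ceiling on those outside the frame altogether, because anyone who returns the 9-month form regains a route. It depends on equal attrition. The 30% limit allows 0.30 × 90 = 27 losses in total, so more than 18 could fall in the intervention arms if they lost more people than control.

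**Step 3. Size of the bias**

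Suppose acceptability were a proportion, p_R among returners and p_N among non-returners. The overstatement would then be p_R − [(1 − d)p_R + d·p_N] = d(p_R − p_N). It is zero if the two groups hold the same view. The document gives neither value. The criterion is also not a proportion: the interviews go through framework analysis and are judged without a threshold. No percentage-point bias can be derived.

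**Step 4. Whether another criterion covers the gap**

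Adherence is recorded (Data management and monitoring) and summarised (Feasibility and proof of concept), but it is not one of the four success criteria. Under the reading of attrition above, someone who never opened the website but posts the questionnaire counts as retained. The 30% limit therefore does not detect abandonment of the programme by people who stay in follow-up.

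**The case against.** A reader might infer that everyone who rejected the programme or left is outside the interview sample, and that the criterion is therefore biased towards success. The document does not support that. Early withdrawers are asked for the next questionnaire, and those who return it can be interviewed. The interview is tied to completing a form, not to completing the programme, so a person who dropped the exercises but stayed in follow-up is eligible. Having received an intervention is not defined as a minimum dose; in context it separates the intervention arms from control. The 9-month interview is a second route.

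Disengagement is also examined elsewhere: website use, text-reported sessions, class attendance and Sway access are recorded, and factors behind drop-out are studied. The physiotherapists are asked about acceptability and barriers, and the qualitative and quantitative data are to be integrated. Heavy loss to follow-up can fail criterion (3), and proceeding also depends on the confidence-interval rule for the difference from control. Finally, an article may leave the details of interview invitation to the full protocol.

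Most of this stands and limits the point to a risk of bias. It does not remove it. The sampling factors and interview timing are stated rules, not gaps left to a fuller document. The adherence summary and the attrition limit show how many people disengaged but do not tell the team why, and adherence carries no weight of its own in the success criteria.

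**Conclusion.** The point holds in a limited form, as a cheap improvement; it does not invalidate the trial. Under the published rule, participants who return neither questionnaire cannot be interviewed, and those who stop or withdraw but return a form are not deliberately sought. Criterion (1) is therefore at risk of bias towards acceptability. That direction is a judgement that non-returners and people who stop are less likely to be satisfied, not something the document shows.

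The size that can be stated is a head count: up to 18 of 60 intervention participants outside the 3-month frame. It assumes attrition at the 30% limit, equal across arms, and defined by questionnaire return. At 10% attrition it is 6 of 60.

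**What to change.** Amend the sampling rule in the nested qualitative study as follows.

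- Add adherence to the purposive factors, using data already collected: classes attended and Sway use for Group E-Rehab; website use and text-reported sessions for My Knee UK. These are gathered at the end of the 12 weeks, in time for 3-month sampling.
- Add discontinuation or withdrawal status as a further factor.
- Let consenting participants who stop, or who return no questionnaire, be invited without a returned form as a precondition.
- Keep the total at about 20 interviews.
- State that criterion (1) is read together with the adherence and attrition data for each arm, and report how many interviewees were low adherers or had stopped.

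The cost is a small amendment. It changes a contact procedure as well as wording, so it needs sponsor approval and then submission to the ethics committee and HRA, as the article's Ethics and dissemination section describes. Recruitment was still open under the current protocol version. Some leavers will decline and their views will remain under-represented, but even a few such interviews would inform the definitive trial.

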### Planned analyses

The intention-to-treat participant population will be used. A full statistical analysis plan (SAP V.1.0, 04 January 2021) was written prior to commencement of recruitment.

#### Sample size

A total sample size of 90 participants (30 per arm), based on established principles for a feasibility study,^39^ will be adequate for evaluating feasibility and collecting sufficient data to inform the sample size in a definitive randomised controlled trial (RCT).

#### Feasibility and proof of concept

As a feasibility study, inferential statistics will be limited. Analysis will focus on descriptive statistics, including measures of frequency (eg, per cent), central tendency (eg, mean, median) and dispersion or variation (eg, SD, IQR, CI estimation), rather than formal hypothesis testing. Data will provide an estimate of recruitment and retention rates and the correlation between baseline and follow-up measurements, to inform the sample size required for a definitive RCT. In line with CONSORT^24^ the choice of primary outcome for the definitive study will be informed by the results of the feasibility study and guided by a previous study,^10^ but candidate variables will be The Western Ontario and McMaster Universities Osteoarthritis Index, pain and physical function domain scores. Published minimum clinically important differences (MCID) reported for the candidate primary outcomes will be used when calculating sample size.^40^ If the difference between the groups favours one or both intervention arms over the control arm, and the two-sided 85% CI around the difference includes the MCID, we will proceed to design a definitive trial provided feasibility criteria are met.^41^ Attrition will be examined to identify any factors that may be systematically affecting drop-out, and continuous measures of adherence within each treatment arm will be summarised. The cost of delivering the e-rehabilitation interventions will be estimated and alongside this, a descriptive report on the use of additional resources (eg, the type of resources, number of contacts and any costs incurred) will be produced.

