#### Outcomes

Patient-reported outcomes covering pain, function, health-related quality of life, coping and catastrophising, and confidence and motivation to do exercises will be measured alongside basic clinical findings at baseline and at the 3-month (12 weeks) and 9-month follow-up timepoints (figure 1 and table 4). These include validated outcome measures used with patients with OA and in knee OA clinical trials.^34–37^ Global change in overall pain and mobility/function and data on the number of contacts made with hospital and community health services, plus any costs incurred due to their knee pain (eg, prescription, travel costs to attend appointments), will be collected at the 3-month and 9-month timepoints. Primary and secondary outcomes have not been specified as this is a feasibility study.

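### The progression condition asks that the 85% CI include the MCID, so an arm whose whole interval is better than the MCID does not meet it

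*Protocol article*

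**What the plan says.** The effect-based condition for moving to a definitive trial stands in the protocol article under Planned analyses, Feasibility and proof of concept. It has three parts:

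- Direction: "If the difference between the groups favours one or both intervention arms over the control arm".
- Interval, followed by feasibility: "the two-sided 85% CI around the difference includes the MCID, we will proceed to design a definitive trial provided feasibility criteria are met".

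The same section says that published MCIDs for the candidate outcomes (the WOMAC pain and physical function domains) will be used for the sample size calculation. It gives no MCID value and no SD.

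The section Feasibility trial outcome lists four joint success criteria: acceptability, a manageable sample size for the definitive trial, attrition of at most 30% at 3 months, and recruitment of at least 40% of eligible patients. The interval condition is not among them. The next sentence reads: "If one or both e-rehabilitation interventions are acceptable, the intention is to develop the protocol for and conduct a definitive RCT".

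**The concern.** An interval that lies wholly on the favourable side of the MCID does not include the MCID. It is the clearest evidence of a worthwhile effect that this trial could give, yet it does not satisfy the printed condition. A feasibility trial needs to know whether a worthwhile effect is still plausible, that is, whether the favourable limit of the interval reaches the MCID. A requirement that the interval contain the MCID adds an upper bound on the estimate, which serves no purpose.

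This is the only effect-based condition in the article. If it is applied as printed, a very effective arm meets it less often than a borderline one. If it is set aside when that happens, the decision is made after seeing the data, which a pre-stated condition is meant to prevent.

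**Working it through.** **Inputs from the protocol article**
- Two-sided 85% CI, so z = z(0.925) = 1.4395 (Feasibility and proof of concept).
- 30 randomised per arm: "A total sample size of 90 participants (30 per arm" (Sample size). The article bases this on general principles for feasibility studies and gives no effect size, SD or power, so there is no calculation to reproduce beyond 3 × 30 = 90.
- Attrition ceiling of 30% at 3 months (Feasibility trial outcome), so 30 × 0.7 = 21 analysed per arm at the limit.

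**Assumptions, because the documents give no figure**
- Outcome in SD units, coded so that a positive difference favours the intervention.
- MCID of 0.4 to 0.5 SD.
- Unadjusted difference in means and a normal approximation.

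**Step 1. Width of the interval.** SE = √(2/n) and half-width h = 1.4395 × SE.
- n = 30: SE = 0.258, h = 0.37.
- n = 21: SE = 0.309, h = 0.44.

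**Step 2. The literal condition.** With estimate D, the condition is met when D > 0 and MCID − h ≤ D ≤ MCID + h. It is missed on the favourable side when D > MCID + h. For n = 30 and MCID 0.5 SD, that means any estimate above 0.50 + 0.37 = 0.87 SD.

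**Step 3. How often the favourable side is missed.** P = 1 − Φ((MCID + h − d)/SE), where d is the true effect. Example with n = 30, MCID 0.4, d = 0.8: (0.4 + 0.372 − 0.8)/0.258 = −0.11, so P = 0.54.

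| n per arm | MCID (SD) | d = MCID | d = 0.6 | d = 0.8 | d = 1.0 |
|---|---|---|---|---|---|
| 30 | 0.4 | 0.075 | 0.25 | 0.54 | 0.81 |
| 30 | 0.5 | 0.075 | 0.15 | 0.39 | 0.69 |
| 21 | 0.4 | 0.075 | 0.21 | 0.44 | 0.69 |
| 21 | 0.5 | 0.075 | 0.13 | 0.32 | 0.57 |

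When d = MCID the result is 1 − Φ(1.4395) = 0.075 whatever the sample size.

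**Step 4. Sensitivity.** Baseline adjustment multiplies the SE by √(1 − ρ²), where ρ is the baseline to follow-up correlation. With ρ = 0.5 and n = 30, h falls to 0.32 SD and the d = 0.8 figures rise to 0.64 (MCID 0.4) and 0.46 (MCID 0.5). A more precise analysis makes the problem worse. A larger MCID makes it rarer: at MCID 0.8 SD, n = 30 and no adjustment, the figure is 0.075 for d = 0.8 and 0.25 for d = 1.0.

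**Step 5. Effect of the corrected wording.** The condition becomes D > 0 and D + h ≥ MCID, so the pass probability is 1 − Φ((max(0, MCID − h) − d)/SE).

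| n = 30, MCID 0.5 SD | As printed | Corrected |
|---|---|---|
| d = 0 | 0.309 | 0.310 |
| d = 0.8 | 0.60 | 0.995 |
| d = 1.0 | 0.31 | above 0.999 |

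For d = 0 over the four combinations in Step 3, the printed rule passes 0.31 to 0.50 and the corrected rule 0.31 to 0.50. The largest single change is from 0.497 to 0.500 (n = 21, MCID 0.4).

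**The case against.** **The sentence is a sufficient condition, not a stop rule.** It says what will happen if the condition is met. It does not say that progression happens only then. A reader might infer that the trial would be stopped on its best result, but the article does not say so: that case is simply not addressed. This stands, and the point is limited to saying that such an arm does not meet the stated condition and has no other stated effect-based route.

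**It is probably a drafting slip, and it matters only for large effects.** Both are fair. At a true effect of 0.6 SD the event has a probability of 13 to 25%, and at the MCID itself 7.5%. A slip in a decision rule still needs correcting.

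**Stronger readings that the article does not support**
- *An ineffective intervention usually passes.* For one arm, outcome and visit the pass rate cannot exceed 50%, because the estimate must favour the arm. Higher rates need passing on any of several outcomes, visits or arms, which the article does not state, together with an assumed MCID. Passing also requires the feasibility criteria. Some leniency is expected of a rule that asks only whether a worthwhile effect remains plausible.
- *The outcome and visit are left open.* The article states that "Primary and secondary outcomes have not been specified as this is a feasibility study" and that "the choice of primary outcome for the definitive study will be informed by the results of the feasibility study". Informing that choice is a declared purpose of the trial, and the visit and MCID value may be fixed in the statistical analysis plan, which was written before recruitment and is not shown. Requiring one particular outcome and visit would be a preference.
- *The trial would proceed on acceptability alone.* The sentence about intention directly follows the four joint criteria and can be read with them. What remains is that those criteria do not mention the interval condition.

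**Conclusion.** The point holds as a wording error in a stated decision condition. As printed, an arm whose whole 85% CI is better than the MCID does not meet it. With an MCID of 0.4 to 0.5 SD, no baseline adjustment and 21 to 30 analysed per arm, this would occur in about 32 to 54% of trials at a true effect of 0.8 SD and 57 to 81% at 1.0 SD, against 7.5% when the true effect equals the MCID. These percentages rest on the assumed MCID and a normal approximation. The logical gap rests on neither.

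The separate placing of the interval condition and the four success criteria is a minor matter of consistency. The two sections can be read together, but a reader has to work out that both apply.

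**What to change.** Before unblinding, change the interval part of the condition so that the two-sided 85% CI *includes the MCID or lies beyond it in the favourable direction*; equivalently, the favourable limit of the interval reaches or exceeds the MCID. Keep the requirements that the estimate favour the intervention and that the feasibility criteria be met. Use the same words in the statistical analysis plan if it repeats the rule.

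In Feasibility trial outcome, add a cross-reference so that the four success criteria and the interval condition are read as one decision.

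The cost is one phrase and one cross-reference, taken through the usual amendment approval by the sponsor and ethics committee. Data collection, sample size and analysis do not change. The revision is not meant to make the rule stricter, and the pass rate of an ineffective arm stays where it is.
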